***Secondary endpoints***

The duration of hospital stay from the time of randomization.The number of ventilator-free days during the first 28 days following randomization.The time to (all-cause) death following the first 10, 28, and 56 days since randomization.The WHO ordinal outcome scale for COVID-19 at days 28, 42 and 56
^24^.Fever clearance time (defined as temperature <37.5°C for 48 hours).Development of acute respiratory distress syndrome (ARDS) defined by the Kigali criteria
^25^.Oxygenation-free days over the first 28 days.Risk of serious adverse events (SAEs).Risk of grade 3 or 4 adverse events (AEs).

### Eligibility criteria

***Inclusion criteria***.

Laboratory-confirmed SARS-CoV-2 infection as determined by RT-PCR, or other commercial or public health assay in any specimen <48 hours prior to randomization, and requiring hospital admission in the opinion of the attending physician.Provides informed consent prior to initiation of any study procedures (or consent provided by an authorized representative).Understands and agrees to comply with planned study procedures.Agrees to the collection of oropharyngeal (OP) swabs and venous blood per protocol.Male or female adult ≥18 years of age at time of enrolment.

***Exclusion criteria***

Intractable seizures of history of uncontrolled epilepsy.History of cardiac arrhythmia requiring on-going anti-arrhythmic therapy.Alanine aminotransferase (ALT) over five times the upper limit of normal.Stage 4 severe chronic kidney disease or requiring dialysis (i.e. eGFR < 30).Anticipated transfer to another hospital that is not a study site within 72 hours.Allergy to any study medication.Chloroquine treatment mandated for any other reason e.g. vivax malaria.Taking a concomitant medication as per
Table 1 which cannot be safely stopped or managed.

**Table 1. T1:** List of concomitant medications with known adverse drug interactions.

Drug	Advice	Reason
Macrolide antibiotics	Avoid	May prolong QT interval
Fluoroquinolones	Avoid	May prolong QT interval
Haloperidol	Avoid	May prolong QT interval
Loperamide	Avoid	May prolong QT interval
Domperidone	Avoid	May prolong QT interval
Amitripylline	Avoid	May prolong QT interval
Fluconazole	Avoid	May prolong QT interval
Ketoconazole	Avoid	May prolong QT interval
Prilocaine	Avoid	Risk of methaemoglobinaemia
Penicillamine	Avoid	Haematological toxicity
Magnesium-based antacids	Avoid	Reduce chloroquine absoprtion
Laronidase	Avoid	Reduces laronidase absoprtion
Dapsone	Avoid	Risk of methaemoglobinaemia
Cimetidine	Avoid	Increases chloroquine levels
Agalsidase	Avoid	Reduces agalsidase levels
Abiraterone	Avoid	May increase serum concentrations of this drug
Conivaptan	Avoid	May increase serum concentrations of this drug
Dabrafenib	Avoid	May decrease serum concentrations of this drug
Dacomitinib	Avoid	May increase serum concentrations of this drug
Enzalutamide	Avoid	May decrease serum concentrations of this drug
Idelasilib	Avoid	May increase serum concentrations of this drug
Mifepristone	Avoid	May increase serum concentrations of this drug
Mitotane	Avoid	May decrease serum concentrations of this drug
Stiripentol	Avoid	May increase serum concentrations of this drug

Note: Pregnant or breast-feeding women are not excluded.

### Study procedures

***Informed consent***. Informed consent to enter into the trial and be randomized must be obtained from all participants (or a person with responsibility e.g. family member/relative as defined by the Vietnam MoH guidelines, if the participants lack capacity), in their own language before enrolment by the site principal investigator (PI) or an appropriately trained clinician
^26^. This should be after explanation of the aims, methods, benefits and potential hazards of the trial and before any trial-specific procedures are performed or any blood is taken for the trial, including for the screening assessment. It must be made completely and unambiguously clear that the participant (or their relative) is free to refuse to participate in or withdraw from all or any aspect of the trial, at any time and for any reason, without incurring any penalty or affecting their subsequent treatment. This will be stated explicitly in the participant information sheet (see
*Extended data*
^27^). If consent was provided by a relative, the participant should be consulted and consent recorded if and when they have the capacity to do so. Signed consent forms must be kept in the investigator site file and if possible from an infection control standpoint, a copy given to the participant or family.

Due to the biohazard of SARS-CoV-2 contaminated documents, special safety provisions must be made for how source documents are collected and stored. In the study sites, the study participants may be treated in an isolation area or a negative pressure room, where paper documents are not allowed to be taken out as presumed contaminates. In such cases, the study will apply other appropriate methods for obtaining valid informed consent as detailed in the Oxford University Clinical Research Unit (OUCRU) informed consent standard operating procedures (SOP). The clinician will document the signing of the consent form in the participant’s medical notes. It may be necessary for a photograph or scanned image of the informed consent signature page to be stored as an “electronic source document” rather than retaining a paper version, which will be destroyed to minimize infection transmission risks. A handheld device (e.g., smartphone) will remain in the high-risk zone for this purpose. This will allow for the information to be transmitted electronically as a PDF for archiving following the OUCRU archiving and destruction of essential documents SOP. The person, who gives consent, will retain a copy of this electronic source document. Where possible a consent form will be re-signed at discharge to ensure a hard copy can be handed to the participant and kept for storage. Copies of the informed consent form in English and Vietnamese are provided as
*Extended data*
^27^.

***Screening and eligibility assessment***. After consent has been obtained from the participant or their relative, clinical information including medical history and examination, and weight will be recorded on the case report form (CRF). Routine tests will also be recorded on the CRF as part of the medical history of the current infection. The screening procedures will take place as soon as possible after the clinicians have identified a potential participant from the study hospitals. Recruitment activities will only occur in an in-patient hospital setting and no activities will be carried out outside of the participating hospitals. The target sample size of 240 participants will be enrolled within an anticipated accrual rate of 6–8 months.

***Randomization and treatment allocation***. Randomization will be 1:1 to either chloroquine or standard of care treatment. Randomization with variable block sizes of four and six will be used to assign subjects to treatment. Randomization will be stratified by recruiting centre and disease severity. The randomization list will be generated according to the OUCRU randomization and drug dispensing SOP. In brief, the study statistician will set up statistical code to generate the randomization list and transfer it to the central study pharmacist. The study pharmacist will change the random seed, i.e. the initialization of the random numbers generator, in the statistical code in order to blind the study statistician and then run the code to prepare the final randomization list for treatment preparation. The randomization list will be password protected and stored on a secure server to which only the study pharmacist has access. Based on the randomization list, the study pharmacist will prepare randomization envelopes and generate identical sealed treatment packs for each study ID and distribute them to the sites in batches as required. Each pack will contain sufficient chloroquine for the 10 days of treatment. Enrolment logs specific to each study site will be used to assign participants to the next available sequential number and corresponding sealed treatment pack.

***Study intervention***. Chloroquine will be administered orally, as tablets. For unconscious participants chloroquine can be crushed and administered as a suspension via a nasogastric tube. A loading dose, administered with food where possible, is given on the first study day. Following the first 24 hours, participants will receive a dose of chloroquine phosphate salt of 500mg once daily until 10 days after randomization (unless they are <53kg, when the dose will be reduced, see
Table 2).

Chloroquine has complex pharmacokinetic properties with an enormous apparent volume of distribution (200–300 L/kg) and a terminal elimination half-life of 1–2 months, so concentrations in plasma (and rapidly exchanging tissue compartments) are determined predominantly by distribution not elimination. Given that EC50 values against the SARS-CoV-2 virus are in the low micromolar range
*in vitro*, which suggests moderate activity, it is likely that relatively high concentrations will be required for maximum effects
*in vivo*. The intervention dose was chosen following evidence review and discussion with healthcare partners. We aimed for an initial loading dose of 10mg/kg base, followed by 5mg/kg base at 6 hours and every 24 hours until 10 days after randomization. The (maximum) dosage used for an adult ≥53 kg is as shown in
Table 2.

**Table 2. T2:** A) Maximum chloroquine dose for an adult ≥53 kg enrolled in the VICO trial. B) Maximum chloroquine dose for an adult <53 kg enrolled in the VICO trial.

**A**			
		Total chloroquine (CQ) dose	
Time	Number of tablets	Chloroquine base	Chloroquine phosphate
Initial dose T=0	4	600mg	1000mg
T=6 hours	2	300mg	500mg
Thereafter	2 once daily for 9 days	300mg once daily	500mg once daily
**B**			
	For an adult 52-45 kg	For an adult <45-38 kg	For an adult <38 kg
Time	Number of tablets	Number of tablets	Number of tablets
Initial dose T=0	3.5	3	2.5
T=6 hours	2	1.5	1.5
Thereafter	2 once daily for 9 days	1.5 once daily for 9 days	1.5 once daily for 9 days

Patients with severe renal impairment or elevated blood transaminases are excluded from the study (see inclusion and exclusion criteria). If an enrolled patient develops cardiac arrhythmia or syncope, chloroquine will be stopped and an electrocardiogram (ECG) performed. Electrolytes (Na, K, Ca, Mg) will be checked and corrected as necessary. Where significant asymptomatic QTc prolongation is identified (>500ms), chloroquine administration will be interrupted, electrolytes checked and corrected, and the drug reintroduced when the QTc is <480ms. Particular care will be taken in those who take other medications, which may prolong QTc.

***Baseline assessment***.

Clinical assessment: All participants will have a full clinical assessment including medical history and examination by the study team. Data collected will include presenting symptoms, duration of illness, past medical history, current medications, and physical examination findings including vital signs (pulse, temperature, blood pressure, oxygen saturations and FiO2), and the results of cardiovascular, respiratory, gastrointestinal and neurological examination in line with standard clinical practice.

Radiology: The results of any radiological imaging (chest X-ray, computed tomography (CT) scan, lung ultrasound) performed during the participant’s illness will be recorded in the clinical reporting form. Participants who have not had a chest X-ray will undergo a chest X-ray on study entry.

Biological specimens and laboratory evaluations: On study entry all participants will have a review of clinical investigations done so far. Where an investigation has been performed within the last 24 hours, the results will be recorded, and they will only be repeated if clinically indicated. Study entry laboratory tests will be performed as per the study schedule below.

***Subsequent assessments***. Participants will have daily assessment as per standard of care while in-patient by the hospital staff. While in-patient the study will collect the following data: peripheral oxygen saturation (pulse oximeter), respiratory rate, and FiO2. The use of a ventilator or other non-invasive ventilation device will be recorded each day. Participants will have clinical assessment recorded as per the trial assessment schedule (see
Table 3). The decision to discharge patients will be at the discretion of the attending physician and will depend upon the clinical status of the patient. According to current standard of care, recovery and hospital discharge is dependent upon the patient having had at least two daily consecutive negative PCR throat/nose swabs. Following discharge, participants will be seen on days 28, 42 and 56 post-randomization.

**Table 3. T3:** Trial assessment schedule.

Procedures	Screening	Enrollment/Baseline (Visit 1)	Follow-Up (Visit 2)	Follow-Up (Visit 3)	Follow-Up (Visit 4)	Follow-Up (Visit 5)	Follow-Up (Visit 6)	Follow-Up (Visit 7)	Daily visits to discharge	Day 28 visit	Day 42 visit	Final Study Visit (Day 56)
Informed consent	x											
Demographics	x											
Medical history	x											
Randomization	x											
Physical exam	x	x	x	x	x	x	x	x	x	x	x	x
Throat/nose swab for viral PCR		x	x	x	x	x	x	x	x			
Vital signs	x	x	x	x	x	x	x	x	x			
Weight		x										
CBC w/diff, plts		x		x		x		x				
Serum chemistry ^a^	x			x		x		x				
Blood store (3-5 mls)		x						x				x
ECG (as indicated) ^b*^		x										
CXR	x								x (discharge)			x
Adverse event evaluation			x	x	x	x	x	x	x	x	x	x
WHO ordinal outcome scale **									x (discharge)	x	x	x
EQ5D questionnaire **										x		x
Estimated total blood volumes ml per day ms	6–10	10–12		10–12		10–12		10–12				3–5
Total blood volume over course of study mls (both clinical and research purposes)												52–63

^a^ Urea, Creatinine, ALT, bilirubin
^b^ Daily ECGs performed if on other medication which can prolong QTc. Additional investigations performed for clinical care can be recorded in the study CRF in order to help understanding of the clinical course. * In HTD and if the patient is in ICU, ECG will be measured continuously every one hour daily for 14 days or until discharge if earlier. ** May be administered by telephone call. Note: if it is impossible for the patient to attend day 28, 42, and 56 visits (e.g. community in lockdown, or hospital closed to non-COVID patients) then follow-up can occur entirely by phone. PCR, polymerase chain reaction; CBC, complete blood count; ECG, electrocardiogram; CXR, chest X-ray; WHO, World Health Organization; ALT, alanine aminotransferase; CRF, case report form; HTD, Hospital for Tropical Diseases; ICU, Intensive Care Unit.

In a subset of participants admitted to HTD we will monitor ECG changes, using real-time monitoring. Participants will have up to one-hour ECG continuous recordings daily. The ECG recording will be downloaded from a standard monitor (GE Careview) and stored electronically. ECG changes (including QT interval) will then be analysed by machine learning.

***Discontinuation of treatment and participation***. Each participant has the right to withdraw from the trial at any time. In addition, the investigator may discontinue a participant from the trial at any time if the investigator considers it necessary for any reason including:
Ineligibility (either arising during the trial or retrospectively having been overlooked at screening)Significant protocol deviationSignificant non-compliance with treatment regimen or trial requirementsAn AE which requires discontinuation of the trial medication or results in inability to continue to comply with trial proceduresDisease progression which requires discontinuation of the trial medication or results in inability to continue to comply with trial procedures
Withdrawal of consentLoss to follow up

If a participant chooses to discontinue their trial treatment (chloroquine), they should always be followed up (providing they are willing) and they should be encouraged not to leave the whole trial. If they do not wish to remain in trial follow-up, however, their decision must be respected and the participant will be withdrawn from the trial. The reason for the participant withdrawing should be ascertained wherever possible. Prior to withdrawing from the trial, the participant will be asked to have assessments performed as appropriate for the final visit although they would be at liberty to refuse any or all components of the assessment.

If a participant withdraws from the trial, the medical data collected during their previous consented participation in the trial will be kept and used in analysis. Consent for future use of stored samples already collected can be refused when leaving the trial early (but this should be discouraged and should follow a discussion). If consent for future use of stored samples already collected is refused, then all such samples will be destroyed following the policies of the institution where the samples reside at the time (local or central storage). Participants may change their minds about stopping trial follow-up at any time and re-consent to participation in the trial. Participants who stop trial follow-up early will not be replaced, as the total sample size includes adjustment for losses to follow-up.

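### The text says the once-daily chloroquine dose is reduced below 53 kg, but Table 2B leaves the 6-hour and daily doses at 45-52 kg the same as at 53 kg and above

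*Protocol article*

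**What the plan says.** All the relevant statements are in the protocol article, under Study procedures, Study intervention.

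- After the first 24 hours, "participants will receive a dose of chloroquine phosphate salt of 500mg once daily until 10 days after randomization", with the qualification "unless they are <53kg, when the dose will be reduced" and a reference to Table 2.
- The basis for the regimen is given per kilogram: "We aimed for an initial loading dose of 10mg/kg base, followed by 5mg/kg base at 6 hours and every 24 hours".
- Table 2A (53 kg and above) gives 4 tablets at time 0, 2 tablets at 6 hours, then 2 tablets daily.
- Table 2B is captioned for adults below 53 kg. Its top column is headed "For an adult 52-45 kg" and gives 3.5 tablets at time 0, 2 tablets at 6 hours, then "2 once daily for 9 days".
- The lower columns of Table 2B give 3, 1.5 and 1.5 tablets (38 to under 45 kg) and 2.5, 1.5 and 1.5 tablets (under 38 kg).

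**The concern.** The weight qualification belongs to the sentence on the once-daily dose; the loading dose is dealt with in the sentence before it. A reader would therefore expect fewer daily tablets for everyone below 53 kg. In the 45-52 kg band the table shows no change in the daily dose. Lighter participants on an unchanged tablet count receive more per kilogram, so the band described as reduced has a higher daily mg/kg than any participant at 53 kg or above.

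At stake is whether the dosing instructions are unambiguous for a drug with a QTc-based interruption rule in the same section, in a trial whose stated primary aim includes safety. Treatment packs are described as identical for each study ID. The weight adjustment therefore seems to depend on the dosing instructions being read correctly; this is an inference, since site dispensing documents are not shown.

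**Working it through.** **Inputs, all from Table 2 and the text around it**

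- First dose at 53 kg and above: "Initial dose T=0 4 600mg 1000mg" (tablets, base, phosphate).
- Daily dose at 53 kg and above: "2 once daily for 9 days 300mg once daily 500mg once daily".
- Tablet counts in Table 2B, as listed above.
- Aim: 10 mg/kg base first, then 5 mg/kg base at 6 hours and every 24 hours.

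**Step 1: tablet strength, and the plan's own daily figure.** 600/4 = 150 mg base and 1000/4 = 250 mg phosphate per tablet. Two tablets are then 300 mg base or 500 mg phosphate, which reproduces the daily dose in Table 2A and in the text.

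**Step 2: the stated reduction at 45-52 kg.** Daily dose: 2 × 150 = 300 mg base, against 300 mg at 53 kg and above. Reduction: 0. The 6-hour dose is likewise 300 mg in both. First dose: 3.5 × 150 = 525 mg against 600 mg. Course: 3.5 + 2 + 9 × 2 = 23.5 tablets against 4 + 2 + 9 × 2 = 24, a difference of 0.5/24 = 2.1%.

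**Step 3: dose per kilogram** = tablets × 150 / weight.

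| Weight (kg) | Tablets: first / 6 h / daily | First dose (mg/kg) | 6 h and daily (mg/kg) | Course (mg/kg) |
|---|---|---|---|---|
| 70 | 4 / 2 / 2 | 8.57 | 4.29 | 51.4 |
| 60 | 4 / 2 / 2 | 10.00 | 5.00 | 60.0 |
| 53 | 4 / 2 / 2 | 11.32 | 5.66 | 67.9 |
| 52 | 3.5 / 2 / 2 | 10.10 | 5.77 | 67.8 |
| 45 | 3.5 / 2 / 2 | 11.67 | 6.67 | 78.3 |
| 44.9 | 3 / 1.5 / 1.5 | 10.02 | 5.01 | 60.1 |
| 38 | 3 / 1.5 / 1.5 | 11.84 | 5.92 | 71.1 |
| 35 | 2.5 / 1.5 / 1.5 | 10.71 | 6.43 | 75.0 |

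**Step 4: comparison.** Against the 5 mg/kg aim, the excess in the 45-52 kg band runs from 5.77/5 − 1 = 15% to 6.67/5 − 1 = 33%. The lowest daily value in the band (5.77, at 52 kg) is above the highest value at 53 kg and over (5.66).

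**Step 5: band limits.** The caption of Table 2B covers all weights below 53 kg, but its top column is labelled only up to 52 kg. A weight such as 52.5 kg has no column unless weights are rounded, and no rounding rule is given. The columns on either side share the 6-hour and daily doses, so only the first dose (3.5 or 4 tablets) depends on how this is read.

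**The case against.** The strongest reply is that the text states no reduced figure of its own. It points to Table 2, and the per-kilogram line is worded as an aim. A reader might infer that sites following the text and sites following the table would give the same participant different doses. The documents do not show this: below 53 kg, Table 2B is the only tablet schedule available. This part of the reply stands.

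The excess over 5 mg/kg also looks like rounding up to the next half tablet, although the article states no such rule. At 45-52 kg the aim equals 5 × 45/150 = 1.5 to 5 × 52/150 = 1.73 tablets, and 2 are given. The excess is not peculiar to this band: 53-59 kg (5.08 to 5.66 mg/kg) and weights below 45 kg exceed the aim too, and participants under 38 kg can reach similar or higher values. The 33% figure applies only at exactly 45 kg. This stands as an explanation of the table, but it does not make the sentence about a reduced daily dose true.

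The higher per-kilogram exposure is confined to the 6-hour and daily doses. At the boundary, the first dose is lower at 52 kg than at 53 kg (10.1 against 11.3 mg/kg) and the course totals are almost equal (67.8 against 67.9 mg/kg).

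A reader might also infer that efficacy or safety results are confounded by weight. They are not: allocation is randomised and the control arm receives no study chloroquine, so weight does not determine the arm. Nor is the open-ended lowest band an error, since it leaves no light adult without a dose.

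Finally, one could read the dose in that sentence as the whole regimen. That reading is met only by half a tablet in 24 and goes against where the clause is placed.

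**Conclusion.** The point holds as a specific contradiction about the study drug. The text says the once-daily dose is reduced below 53 kg; for 45-52 kg the table reduces it by nothing. The daily dose there is 5.8 to 6.7 mg/kg base, 15% to 33% above the stated aim and above the 5.7 mg/kg maximum at 53 kg and over. The top band label also fails to meet the 53 kg limit.

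This rests on a tablet strength of 150 mg base, which Table 2A gives consistently, and on reading the qualification as applying to the daily dose, as the sentence is built. Table 2 is captioned as a maximum, but the article gives no other rule that would produce a lower daily dose.

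The primary endpoint, the sample size and the randomised comparison are unaffected. What is affected is the clarity of the dosing instruction and the variation of per-kilogram exposure within the chloroquine arm. The correction is cheap and bears on participant safety, so it is worth making. Nothing in the documents shows that any site has dosed differently because of it.

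**What to change.** The sponsor should reconcile three things so that they agree at every weight: the sentence on reduction below 53 kg, the per-kilogram aim, and Tables 2A and 2B. If rounding to half tablets explains the table, the rule should be stated. The top band of Table 2B should be relabelled so that it meets 53 kg without a gap. The sponsor should also confirm that the dosing instructions held at the sites match the reconciled version. Which dose applies in each band is for the clinical team to decide.

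The cost is a correction to the protocol and pharmacy instructions and a notice to sites. The Study status section reports two participants enrolled, so the correction would come early in recruitment.

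### No QTc entry limit and no ECG tied to randomisation or first dose, so a patient already above the protocol's 500 ms interruption threshold can be randomised and loaded

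*Protocol article*

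**What the plan says.** Under Study intervention, the protocol article gives a rule for asymptomatic QTc prolongation: "Where significant asymptomatic QTc prolongation is identified (>500ms), chloroquine administration will be interrupted". Electrolytes are then checked and corrected, "and the drug reintroduced when the QTc is <480ms".

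The inclusion and exclusion lists contain no QTc or ECG criterion. The only cardiac exclusion is "History of cardiac arrhythmia requiring on-going anti-arrhythmic therapy". A separate exclusion covers Table 1 co-medications that cannot be safely stopped or managed; eight entries in that table are there because they may prolong the QT interval. The Expectedness text lists QT prolongation among the known toxicities of chloroquine.

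Table 3 has one ECG row, labelled "ECG (as indicated"), with a single mark in the Enrollment/Baseline (Visit 1) column. Randomization is marked in the Screening column. The footnotes add two kinds of monitoring: "Daily ECGs performed if on other medication which can prolong QTc", and "In HTD and if the patient is in ICU, ECG will be measured continuously every one hour daily for 14 days" or until discharge if that is earlier. The text below the table describes the real-time recording as applying to a subset of participants admitted to HTD.

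The Baseline assessment text covers clinical examination, radiology and laboratory tests. For radiology it is explicit: "Participants who have not had a chest X-ray will undergo a chest X-ray on study entry". It has no matching sentence for an ECG.

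**The concern.** The protocol treats a QTc above 500 ms as a reason to stop giving chloroquine, but it has no corresponding check before the drug is started. The course is front-loaded, with a double dose at T=0 and a further dose at 6 hours, and interrupting the drug later cannot take back what has been given. The Study intervention text itself gives a terminal half-life of 1 to 2 months.

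Asymptomatic prolongation is found only by recording and reading an ECG. If the baseline ECG is optional, or is done but read after dosing, the interruption rule acts too late to protect the patient during loading. What is at stake is participant safety and the coherence of the eligibility criteria with the protocol's own threshold. The sample size and the primary analysis are not affected.

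**Working it through.** **1. Order of events in Table 3.**

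| Item | Where marked |
|---|---|
| Randomization | Screening |
| Serum chemistry (includes creatinine and ALT) | Screening, then later visits |
| ECG, as indicated | Visit 1 only |

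The laboratory tests behind the renal and hepatic exclusions are marked alongside randomisation and can inform it. The ECG is marked in the next column.

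**2. Is the Visit 1 ECG for everyone?** Two readings are possible. In the first, every patient has a baseline ECG and only repeats are as indicated. In the second, the ECG is discretionary throughout. The Baseline assessment text does not settle it, since it makes a chest X-ray universal and does not mention an ECG. On either reading, no sentence requires the result to be known before randomisation, before T=0 or before T=6 hours.

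**3. Does the QTc rule prevent starting the drug?** Its verbs are to interrupt and to reintroduce. Both presuppose that dosing has begun. It is not among the exclusion criteria.

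**4. Who is covered by the additional monitoring?** Take the HTD and intensive-care footnote at its broadest, as covering anyone at HTD and anyone in intensive care, and add patients on other QT-prolonging drugs. That still leaves the patient at Cu Chi or Can Gio who is outside intensive care and takes no such drug. This patient has no scheduled ECG after Visit 1. For covered patients too, no reading before the first dose is stated.

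**5. How much drug is given during loading?** Inputs are from Table 2. Part A gives 600 mg base as 4 tablets, so one tablet is 600/4 = 150 mg base. Share of course = (T=0 + T=6 h tablets) / (those tablets + 9 daily doses).

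| Weight | Loading tablets | Total tablets | Loading / total, mg base | Share |
|---|---|---|---|---|
| ≥53 kg | 4 + 2 = 6 | 6 + 9×2 = 24 | 900 / 3600 | 25.0% |
| 52–45 kg | 3.5 + 2 = 5.5 | 5.5 + 9×2 = 23.5 | 825 / 3525 | 23.4% |
| <45–38 kg | 3 + 1.5 = 4.5 | 4.5 + 9×1.5 = 18 | 675 / 2700 | 25.0% |
| <38 kg | 2.5 + 1.5 = 4 | 4 + 9×1.5 = 17.5 | 600 / 2625 | 22.9% |

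So 23% to 25% of the course is given within 6 hours in every weight band. This measures exposure. It is not an estimate of QT risk.

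**6. Does the pilot close the gap?** The Study design section gives the 10-patient pilot the same entry criteria and procedures as the trial, so the pilot has the same gap.

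**The case against.** The strongest reply is that Table 3 does schedule an ECG at baseline, and baseline ordinarily means before treatment. Adverse event evaluation starts only at Visit 2, which fits that reading. A clinician who saw a QTc above 500 ms at that visit would hardly take the interruption rule as permission to load. The rule is triggered wherever prolongation is identified and, unlike the preceding sentence on arrhythmia and syncope, does not require new onset. The arrhythmia exclusion, the Table 1 exclusions and the instruction to take particular care with QT-prolonging drugs narrow the population further. A condensed article may also leave operational detail to the full protocol.

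Much of this stands. A reader might infer that no baseline ECG is planned; the documents do not support that, because the row is ambiguous and not empty. A reader might also call this an outright contradiction. It is not, since a stopping rule and an entry criterion need not match.

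What does not fall away is the order of events. Even if clinicians apply the rule at baseline, the printed schedule has already randomised the patient, who then remains in the chloroquine arm with the drug withheld. The article prints its eligibility lists and schedule as complete lists, so the gap lies between printed rules and is not just an omitted detail.

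**Conclusion.** The point holds as a safety and eligibility gap. Following the printed criteria and schedule, a patient with QTc above 500 ms can be randomised and can receive both loading doses, 900 mg base or 25% of the course at 53 kg or more, without any stated rule being broken. This rests on the Table 3 columns as printed and on reading interruption as applying to a drug already started.

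Three stronger conclusions are tempting, and the documents do not support them:

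- **Entry limit of 480 ms.** A reader might infer this from the restart rule. That figure governs re-challenge after prolongation above 500 ms. The protocol lets patients between 480 and 500 ms continue treatment, so using it at entry would exclude patients whom the protocol would keep on drug. That is a trade-off for the sponsor to weigh.
- **A count of affected patients.** The documents give no prevalence of prolonged QTc at entry, so any such number would only restate an assumption.
- **Bias in the treatment comparison.** A reader might point to the per-protocol set, which drops patients with less than a week of chloroquine. The main analysis is by randomised arm in the full analysis population, the protocol provides for restarting the drug, and the one-sided per-protocol rule applies to any early stop. It is a separate matter that a baseline ECG would not remove.

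**What to change.** Make two edits.

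1. In Table 3, state that the baseline ECG is done in all participants in both arms and read before randomisation, with the as-indicated qualifier applying only to repeats. Moving the mark to the Screening column and adding one sentence to Baseline assessment, parallel to the chest X-ray sentence, would make this clear.
2. In the exclusion criteria, add that a patient with QTc above 500 ms is not randomised. Allow electrolytes to be corrected and the patient to be re-screened.

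The cost is small. The ECG is already in the schedule and the threshold is the sponsor's own. Every patient has the ECG and it is read earlier, which adds some work before allocation at the field sites. A few patients will be delayed or excluded. A delayed patient may occasionally need a repeat test, because infection must be confirmed "in any specimen <48 hours prior to randomization".
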